### Sample size estimation

The sample size calculation was based on previous findings, and the proportion of patient with a mRS of 0–2 at 90 days of 41% was estimated for the placebo group, and of 58% was assumed for the glibenclamide-treated group [11]. When half of the planned subjects finish their 90-day follow up an interim analysis will be conducted and the O’Brien - Fleming method will be used to control the type I error. Using nQuery + nTerim 4.0 (Statistical Solutions Ltd., Farmer’s Cross, Cork, Ireland) with a 2-sided χ^2^ test, a two-sided significance level of 0.05, a power of 80%, the O’Brien - Fleming alpha spending function and a dropout rate < 10%, 153 patients are required in each group, for a total sample size of 306.

### Statistical analyses

The primary outcome will be compared between 2 groups using χ^2^ tests, and the confidence interval of the rate difference will be calculated using the Newcombe’s method [27]. Common risk difference for multiway 2 × 2 tables stratified by endovascular treatment and baseline NIHSS score (≥ 14 or < 14) will also be reported. The Mantel-Haenszel estimate, confidence limits, and test for the common risk differences by using Mantel-Haenszel stratum weights and the Sato variance estimator will be used. When half of the planned subjects are recruited and their 90-day follow up are finished, interim analysis will be conducted by a selected biostatistician. O’Brien - Fleming method will be used to control the Type I error. The trial will be stopped early when the primary outcome of the interim analysis significantly favors or contradicts the usage of glibenclamide.

For baseline variables and other outcomes, comparisons between normally distributed continuous variables, expressed as mean ± SD, will be performed using 2-sample t tests; non-normally distributed continuous variables, presented as median and interquartile range, will be analyzed using Wilcoxon rank sum tests. Pearson χ^2^ or Fisher exact tests will be used, as appropriate, for categorical data, which will be expressed as percentages. For secondary outcomes mRS shift and MMP-9, mixed effect model will also be used.

For safety analysis, all adverse events and serious adverse events, including deaths, will be summarized by body systems in terms of frequency, severity, and relatedness to the study drug using the MedDRA codes. Frequencies of adverse events from these two groups will be reported. Pearson χ^2^ or Fisher exact tests will be used, as appropriate, to compare the incidence of adverse events between the two groups.

Subgroups analyses will be performed according to pre-defined design variables, such as: sex, age (≤ 60 years vs. 61–74 years), endovascular treatment, NIHSS grade (4–13 vs. 14–25), time window in rtPA thrombolysis (< 3.5 h vs. 3.5–4.5 h), and study drug treatment time (< 6 h vs. 6–10 h).

The primary and secondary end points will be analyzed based on the modified intention-to-treat (mITT) population which excludes those patients who do not receive treatment or control and has no efficacy outcome data, and those subjects who are diagnosed with posterior circulation occlusion alone after being included. Per-protocol patients who finish the treatment protocol with good compliance, will also be analyzed as a sensitive analysis. Safety analyses will be done in patients receiving allocated treatment. Last observation carried forward method will be used to deal with the missing data of primary outcome, and multiple imputation method will also be used as sensitive analysis. All analyses will be 2-tailed and a significance level of 0.05 will be used for all outcomes. All data analyses will be performed using SAS version 9.4 (SAS Institute, Cary, NC).

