### Randomization and blinding

Eligible patients will be allocated using a web-based 1:1 randomization process. The randomization will be stratified by center, and the Pocock and Simon’s minimization method will be implemented to balance two important prognostic factors, endovascular treatment and baseline NIHSS score (≥14 or < 14). The study drugs, glibenclamide and placebo, are manufactured by Succhi Pharmaceutical (Zhongshan, China) following Good Manufacturing Practices regulations, and are coded and concealed by an independent biostatistician. In this manner, all trial participants, care providers and outcome assessors will be blinded to intervention allocation.

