### Treatment

An overview of the study flowchart is presented in Fig. 1. Intravenous rtPA treatment will be initiated at a standard dose and regimen (0.9 mg/kg, initial bolus of 10% of the total dose and the remaining dose as an intravenous infusion lasting over 60 min) following current clinical guidelines [14]. When a patient meets all the inclusion/exclusion criteria and signs the informed consent, randomization will be performed and the study drug will be given as soon as possible after starting the infusion of rtPA treatment. Based on previous studies, the target time from symptom onset to the start of study drug is ≤10 h [9, 15]. The study drug (glibenclamide/placebo, 2.5 mg/pill) will be evenly divided with a pill splitter and given orally by trained hospital nurses. If the patient is unable to ingest orally due to dysphagia or altered consciousness, the study drug will be grinded and dissolved with water and administered through a nasogastric tube, followed by flushing down the nasogastric tube with water. In order to achieve a steady-state concentration rapidly, a loading dose of 1.25 mg will be given, followed by 0.625 mg every 8 h for 5 days. The total given dose will be 10 mg. Since the optimal dosage of oral glibenclamide in treating AIS remains unclear, in this study we use a relatively low-dose regimen differed from that of intravenous preparations [16], with combined consideration of its high bioavailability and hypoglycemic potency. In our preliminary study, the current dose regimen of oral glibenclamide was well tolerated, associated with less brain edema, and did not increase the risks of early death, hypoglycemia, and early neurological deterioration [17]. In addition, our unpublished data has shown that this dosing regimen was able to result in average steady-state plasma glibenclamide levels of 19 ng/mL, which is not inferior to the concentrations reached by the effective therapeutic dose in rats [16].

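### The lead test of the primary outcome is an unadjusted chi-square although allocation is balanced on EVT and NIHSS; promoting the already planned Mantel-Haenszel test would gain efficiency at no cost in patients

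*Protocol article*

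**What the plan says.** **Allocation** (Protocol article, Randomization and blinding): "The randomization will be stratified by center, and the Pocock and Simon’s minimization method will be implemented". The same sentence gives the purpose: "minimization method will be implemented to balance two important prognostic factors, endovascular treatment and baseline NIHSS score", with NIHSS cut at 14.

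**Lead analysis** (Statistical analyses): "The primary outcome will be compared between 2 groups using" chi-square tests, and the interval for the rate difference is to be obtained by Newcombe's method. Neither the test nor the interval uses an allocation factor. The Sample size estimation section is built on a two-sided chi-square test as well.

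**Stratified analysis** (same paragraph): "Common risk difference for multiway 2 × 2 tables stratified by endovascular treatment and baseline NIHSS score (≥ 14 or < 14) will also be reported". This is a full inferential analysis, since the next sentence specifies "The Mantel-Haenszel estimate, confidence limits, and test for the common risk differences by using Mantel-Haenszel stratum weights and the Sato variance estimator". It has four strata and does not include centre.

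**Which one decides.** The order and wording place the stratified analysis second. The early-stopping rule turns on a significant primary outcome at the interim but does not say by which of the two tests.

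**The concern.** Balancing the arms on a prognostic factor removes that factor's contribution to the chance variation of the treatment difference. An unadjusted chi-square still counts that contribution in its variance. Its p-value is then too large on average and its interval too wide. A test stratified by the balancing factors uses the variance that the design actually produces.

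The protocol's own premise is that EVT and NIHSS matter for outcome. On that premise the lead test is the less efficient of the two tests already in the plan. Two tests of one outcome, with no explicit statement of which governs the interim and final decisions, also leave room for dispute when they disagree.

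**Working it through.** **1. The plan's own figure.** Inputs from Sample size estimation: 41% vs 58%, two-sided α 0.05, power 80%, chi-square, O'Brien-Fleming spending with one interim at half, dropout below 10% (10% used here).

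n per group = [z₀.₉₇₅·√(2p̄q̄) + z₀.₈₀·√(p₁q₁ + p₂q₂)]² / δ²

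- p̄ = 0.495, so 1.960 × √0.49995 = 1.386
- p₁q₁ + p₂q₂ = 0.2419 + 0.2436 = 0.4855, so 0.8416 × √0.4855 = 0.586
- (1.386 + 0.586)² / 0.17² = 134.6, rounded up to 135
- Two-look O'Brien-Fleming inflation of 1.0078 (assumed; not in the document): 136.05, rounded up to 137
- 137 / 0.90 = 152.2, rounded up to **153**, which matches the protocol

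The fixed-sample chi-square power at 137 evaluable per group is 80.7%. The trial therefore reaches its target with the test as planned.

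**2. Why the chi-square is conservative, by hand.** Assume 40% of patients have NIHSS ≥14 and good-outcome rates of 55% (low NIHSS) and 20% (high NIHSS). The marginal rate is 0.6 × 0.55 + 0.4 × 0.20 = 0.41, the protocol's placebo rate.

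- Variance used by the chi-square: 0.41 × 0.59 = 0.2419
- Variance left under perfect balance: 0.6 × 0.2475 + 0.4 × 0.16 = 0.2125
- Ratio 0.2125 / 0.2419 = 0.878, square root 0.937
- Type I error: P(|Z| > 1.960 / 0.937 = 2.091) = 3.7%

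With rates of 50%/27% the ratio is 0.2288 / 0.2415 = 0.947 and the type I error 4.4%. With 58%/15% it is 0.1972 / 0.2415 = 0.816 and 3.0%. These figures assume perfect balance on NIHSS alone. Minimisation balances imperfectly, so somewhat higher values are expected in simulation.

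**3. Simulation.** From the protocol: 8 centres, 1:1 allocation, minimisation within centre on EVT and NIHSS, marginal rates 41% and 58%. Assumed: biased-coin probability 0.8 and the prognostic strengths below. All tests are fixed-sample at two-sided 5%; the interim was not simulated.

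Set A: 274 evaluable patients, 35% with NIHSS ≥14, 25% base EVT rate, unequal centres, 20,000 runs per scenario. MH-4 is the planned EVT × NIHSS test with Sato variance; MH-32 adds centre.

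| NIHSS log-OR | Type I, chi-square | Type I, MH-4 | Power, chi-square | Power, MH-4 | Power, MH-32 |
|---|---|---|---|---|---|
| 0 (not prognostic) | 4.8% | 5.0% | 80.3% | 81.2% | 79.7% |
| 0.8 (weak) | 4.5% | 5.0% | 81.0% | 82.8% | 81.3% |
| 1.5 (moderate) | 3.9% | 4.9% | 81.5% | 85.2% | 84.3% |
| 2.2 (strong) | 3.1% | 4.7% | 82.8% | 88.6% | 88.0% |

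Set B: 276 patients, 40% with NIHSS ≥14.

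| NIHSS log-OR | Type I, chi-square | Power, chi-square | Power, MH-4 | Difference |
|---|---|---|---|---|
| 0.8 | 4.6% | 80.5% | 82.5% | 2.0 points |
| 1.5 | 3.8% | 81.5% | 85.5% | 4.0 points |
| 2.2 | 3.2% | 81.9% | 88.8% | 6.9 points |

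**4. Centre.** In Set A, going from 4 to 32 strata cost 1.5, 1.5, 0.9 and 0.6 points, in the order of the table. It helped only under a large assumed centre effect (SD 0.7 on the logit scale, moderate NIHSS effect): 86.1% vs 85.5%.

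**5. How often the choice matters.** In separate runs under the Set B conditions and the design effect, the two tests disagreed at the 5% level in 2.6%, 4.2% and 7.4% of trials (weak, moderate, strong). Nearly always the Mantel-Haenszel test was significant and the chi-square was not.

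**The case against.** **The plan is consistent and sufficient as it stands.** The trial was sized on a chi-square, it leads with a chi-square, and that test meets the 80% target. Any departure in type I error is downward. The stratified test is already prespecified, so the allocation factors are not ignored altogether. All of this stands, and it makes the point one of efficiency and of which analysis leads. A reader might infer that the trial is underpowered or its primary p-value invalid; the documents support neither.

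**The size is assumed.** The protocol gives no outcome rates by NIHSS or EVT, no stratum frequencies and no biased-coin probability. This stands too. The loss is conditional on prognostic strength and nearly vanishes without it. What remains is that the protocol itself calls the factors prognostic.

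**Centre.** Because allocation is stratified by centre, a reader might infer that centre belongs in the confirmatory strata and would add power. Step 4 of the working shows a small cost unless centre effects are large, and nothing in the protocol says that they are.

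**EVT timing.** The Treatment section says "randomization will be performed and the study drug will be given as soon as possible after starting the infusion of rtPA treatment", so a reader might infer that the EVT stratifier is a post-randomisation variable. The text does not show this. Minimising on EVT requires a value at randomisation, and nothing says that a later value would replace it. Stating which value is used is a clarification, not the correction of a shown error.

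**Conclusion.** The point holds as an efficiency improvement. On the protocol's premise that EVT and NIHSS are prognostic, the lead chi-square is conservative, with type I error of about 4.6% for weak and 3.2% for strong assumed effects. It forgoes about 2 to 7 points of power against a test already in the plan. Without prognostic value the gap is 0.9 points in Set A.

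These sizes rest on the assumed NIHSS effect, stratum frequencies and 0.8 coin, and on fixed-sample tests. The direction follows from the design; the amount cannot be fixed from the document. Neither the sample size of 306 nor the validity of the planned analysis is in question.

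**What to change.** In Statistical analyses:

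- Name the Mantel-Haenszel common risk difference with Sato variance, its confidence limits and its test, as the single confirmatory analysis of the primary outcome at both the interim and the final look.
- Define the four strata as NIHSS group (≥14 or <14) by EVT status as entered in the web system at randomisation.
- Keep the chi-square test and Newcombe interval as supportive.
- Leave centre out of the confirmatory strata. A centre-stratified version can serve as a sensitivity analysis.

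**Cost:** a change of wording, with no extra patients or data. It also changes the test that the O'Brien-Fleming boundary is applied to, so it should be made before any unblinded look. The sample size can stay at 306; a line should note that it was calculated for the chi-square, which had the lower power in every scenario simulated.

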### Outcome assessments

All patients will be followed up by trained neurologists blinded to study data. The primary and secondary endpoints of this study are summarized in Table 2. The SE-GRACE trial is designed with combination of clinical, imaging and biochemical outcomes to provide information about clinical benefits and relevant mechanism of action. Subjects will be followed up in person or through telephone review at 30 ± 7 days, 90 ± 14 days (the primary end-point), 180 ± 30 days and 360 ± 30 days after the onset of AIS, using modified Rankin Scale (mRS), Barthel Index (BI) and Informant Questionnaire on Cognitive Decline in the Elderly (IQCODE) (Fig. 1) [21, 22]. The primary outcome will compare the proportion of “good outcome” in the glibenclamide-treated group to the placebo group, with good outcome defined as a patient with a mRS of 0–2 at 90 days after the onset. The BI is a 10-item measure of activities of daily living which is frequently used in clinical practice and as a trial outcome measure in stroke, with a total score of 60 to 100 generally regarded as good outcome [23]. The IQCODE is an informant-based assessment tool for diagnosis of poststroke dementia and/or multidomain cognitive impairment, with a pooled sensitivity of 0.81 and specificity of 0.83 in a recent a systematic review [22]. The cutoff value of IQCODE for diagnosing poststroke dementia is generally considered to be > 3.4 [21, 22].

**Table 2 Tab2:** Primary and secondary endpoints of the trial

Outcome	Description
Primary outcome	The ratio of mRS ≤ 2 at 90 days after the stroke onset
Secondary outcome	1. The ratio of NIHSS decreased ≥4 points at 7 days after the stroke onset
	2. The ratio of parenchymal hemorrhagic transformation in cranial CT within 96 h after the onset
	3. The ratio of midline shift ≥6 mm in cranial CT within 96 h after the onset
	4. The mRS shift at 90 days after the onset
	5. The ratio of Barthel Index of 60–100 points at 90 days after the onset
	6. The proportion of Informant Questionnaire on Cognitive Decline in the Elderly (IQCODE) of ≤3.40 at 6 months and 1 year after the stroke onset
	7. The serum concentration of MMP-9 at baseline, and at 24, 48, and 72 h after onset
Safety outcome	1. The mortality at 90 days after the onset
	2. The ratio of neurological deterioration (NIHSS increased ≥4 points) within 24 h after the onset
	3. The incidence of hypoglycemia (random blood glucose < 3.9 mmol/L)

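### The 90-day mRS shift has only generic unadjusted tests and a mixed model of unstated type; an adjusted proportional-odds model with a common odds ratio would be better

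*Protocol article*

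**What the plan says.** Table 2 (Outcome assessments) lists secondary outcome 4 as "The mRS shift at 90 days after the onset". The mRS itself is collected at "30 ± 7 days, 90 ± 14 days (the primary end-point), 180 ± 30 days and 360 ± 30 days after the onset".

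The Statistical analyses section then gives rules by type of variable for baseline data and all outcomes other than the primary:

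- two-sample t tests for normally distributed continuous variables;
- for the rest of the continuous data, "non-normally distributed continuous variables, presented as median and interquartile range, will be analyzed using Wilcoxon rank sum tests";
- Pearson chi-square or, in the article's words, "Fisher exact tests will be used, as appropriate, for categorical data, which will be expressed as percentages".

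It does not say which class the mRS belongs to. The one method tied to this outcome by name comes next: "For secondary outcomes mRS shift and MMP-9, mixed effect model will also be used".

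Under Randomization and blinding, "The randomization will be stratified by center", and minimisation balances "two important prognostic factors, endovascular treatment and baseline NIHSS score", the latter cut at 14. For the primary outcome, the Statistical analyses section adds to the chi-square test a Mantel-Haenszel common risk difference stratified by these two factors. No counterpart is stated for the mRS shift.

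**The concern.** The shift analysis uses the whole mRS scale and will be read next to the 0–2 dichotomy. Three things about it are weakly fixed.

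- **Adjustment.** The article itself calls NIHSS and endovascular treatment important for prognosis, and both are known for every randomised patient. The tests named for outcomes of this kind use neither.
- **Model.** One label covers two data structures. MMP-9 is measured at baseline, 24, 48 and 72 h, so a mixed model is natural there. The mRS shift is defined at day 90 only. A model across all four mRS visits and a model of day 90 with centre as the random effect would both fit the wording, and they do not give the same estimate unless a day-90 contrast is specified.
- **Effect measure and order.** No odds ratio or other summary is named. Nothing says whether the generic test or the mixed model is the main analysis, and 0.05 applies to all outcomes.

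At stake are some power and a predefined effect estimate for this outcome. The validity of the trial is not in question.

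**Working it through.** **1. The article's own figure.** Inputs from Sample size estimation: 41% versus 58%, two-sided 0.05, power 80%, one interim look at half the subjects with O'Brien-Fleming spending, dropout 10% (the stated upper limit).

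n per arm = [1.960·√(2·0.495·0.505) + 0.842·√(0.41·0.59 + 0.58·0.42)]² / 0.17² = (1.386 + 0.586)² / 0.0289 ≈ 134.6, so 135.

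The two-look design (bounds 2.772 and 1.979) inflates this by 1.0087: 135 × 1.0087 ≈ 136.2, so 137. Dropout: 137 / 0.90 ≈ 152.2, so 153 per arm and 306 in total. Rounding up at each step, the stated figure is reproduced. It rests on the binary primary outcome, so the analysis of the mRS shift does not enter it.

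**2. Implied common odds ratio.** (0.58/0.42) / (0.41/0.59) = 1.381 / 0.695 = 1.99.

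**3. What the lack of adjustment costs.** Simulation with 138 evaluable patients per arm (153 × 0.90 = 137.7) and 1,000 trials per scenario, under

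logit P(mRS ≤ k) = c_k + log(OR)·treatment − b_N·[NIHSS ≥ 14] − b_E·[endovascular].

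Assumptions that are not in the documents:

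- placebo mRS 0 to 6 distributed 10/16/15/16/18/10/15%, so that 0–2 totals 41%;
- 35% with NIHSS ≥ 14 and 25% with endovascular treatment, both balanced exactly between arms;
- proportional odds, no centre effect, and the values of b_N and b_E below.

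Shift is read as a comparison of the 90-day distribution over 0–6. The comparison is a Wilcoxon test against a likelihood-ratio test in a proportional-odds model adjusted for both factors, each at two-sided 0.05.

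| Conditional OR | b_N, b_E | Wilcoxon | Adjusted | Gap (points) | Unadjusted OR |
|---|---|---|---|---|---|
| 1.7 | 0.7, 0 | 0.681 | 0.698 | 1.7 | 1.69 |
| 1.7 | 1.5, 0.5 | 0.644 | 0.726 | 8.2 | 1.63 |
| 1.7 | 2.0, 0.5 | 0.573 | 0.700 | 12.7 | 1.57 |
| 1.99 | 0.7, 0 | 0.876 | 0.895 | 1.9 | 1.97 |
| 1.99 | 1.5, 0.5 | 0.853 | 0.904 | 5.1 | 1.86 |

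The strongest prognostic setting at 1.99 was not completed. The Monte Carlo standard error of a power near 0.7 is √(0.7·0.3/1000) ≈ 1.4 points.

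**4. Validity.** With no treatment effect, Wilcoxon rejected in 4.9%, 2.8% and 2.4% of trials across the three prognostic settings, and the adjusted model in 4.8% to 4.9%. Balancing strong prognostic factors and then ignoring them makes the rank test conservative. It does not inflate type I error.

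**5. Reading the last column.** The unadjusted odds ratio is nearer 1 because odds ratios change when a prognostic factor is averaged over. That is a different estimand, not a bias. It also means that entering 1.99, a ratio of overall proportions, as the conditional value slightly understates the effect the trial was sized on.

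**The case against.** The case on the other side is substantial. The article is condensed, and the link, covariates and random effects of a model for a secondary outcome are ordinary material for an analysis plan that is not shown. Nothing in the text is false or contradictory on this point. Mixed models also cover ordinal outcomes, patients are clustered in 8 hospitals, and the remedy proposed here is itself a mixed model, so the authors may already intend it.

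Much of that stands, and several stronger readings that a reader might infer are not supported:

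- *That Wilcoxon is the stated test.* It is the likely one, but the article assigns it to non-normal continuous data and leaves the mRS unclassified. The simulation therefore compares against a probable test, not a declared one.
- *That a mixed model cannot fit this outcome, or that an adjusted ordinal model has been ruled out.* A cumulative-logit model with centre as a random effect is compatible with the wording, as is a longitudinal model with a day-90 contrast.
- *That there will be no interpretable estimate.* Any fitted model yields one; the article only fails to say which.
- *That the gain is very large.* A smaller simulation (300 trials per setting, odds ratio 1.8, NIHSS as a continuous score) gave 72% versus 80%, and 56% versus 76% with a stronger NIHSS effect. The 20-point gap depends on a coefficient found nowhere in the documents and on holding the conditional odds ratio fixed, which lowers the overall effect as the coefficient rises.

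What the objection does not remove is the following. The closing paragraph of the Discussion presents the article as the description of the planned analysis, meant to limit data-driven results. The generic tests it names are all unadjusted, and the article adjusts for the same two factors in its primary outcome. A concrete better method is available from data already collected.

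**Conclusion.** The point holds as a minor improvement to a secondary analysis. For the 90-day mRS shift, the article states an unadjusted generic test, probably Wilcoxon, and a mixed model whose type, covariates and effect measure are open. The unadjusted test is valid but less efficient: about 2 to 13 points of power across the scenarios run, and 2 to 5 points, with power above 80% either way, at the implied odds ratio of 1.99. These sizes rest on the assumed prognostic strengths, the assumed mRS distribution and proportional odds. The direction needs only that baseline NIHSS or endovascular status predicts outcome, which the article itself asserts. The sample size of 306 and the primary analysis are untouched.

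**What to change.** In Statistical analyses, name one main analysis for secondary outcome 4: a proportional-odds (cumulative-logit) model of the 90-day mRS (0–6) with treatment, baseline NIHSS and endovascular treatment as entered at randomisation as fixed effects, and centre as a random effect. Report the common odds ratio with its 95% CI. Keep the unadjusted rank test as a supporting analysis, or as the fallback if proportionality clearly fails, and say beforehand what would count as failure. Describe the mixed model for the repeated MMP-9 values in a separate sentence.

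The cost is analysis wording only, with no new data and no change in sample size. The one small downside is a proportional-odds assumption that has to be checked.

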### Patient inclusion and exclusion criteria

Eligibility criteria are presented in Table 1. Patients aged 18 to 74 years with AIS and a symptomatic anterior circulation occlusion with a deficit on the National Institute of Health Stroke Scale (NIHSS) of 4 to 25 points, treated with intravenous rtPA within the first 4.5 h of clinical onset, are eligible for participation in this trial. The exclusion criteria are modified from that set in the previous study [15]. The diagnosis of AIS is based on cranial CT scan and clinical manifestations. However, since not all patients will receive brain MRI examination or angiography before randomization, the diagnosis of anterior circulation AIS will base largely on clinical symptoms and signs, and thus some patients with posterior circulation occlusion alone may be mistakenly included before an MRI examination or angiography done. Therefore, once these subjects are diagnosed with posterior circulation occlusion alone after being included, they would stop using the study drugs immediately, but continue to receive other standard treatment and follow-up. These participants will be excluded from the modified intent-to-treat population when performing statistical analysis. Site investigators are responsible for enrolling participants, obtaining informed consent and managing randomization.

**Table 1 Tab1:** Inclusion and exclusion criteria for the SE-GRACE trial

Criteria	Description
Inclusion criteria	1. Clinical diagnosis of acute ischemic stroke in the MCA territory (PCA and/or ACA territory involvement in addition to primary MCA territory stroke is acceptable)
	2. Aged ≥18 and ≤ 74 years
	3. A baseline NIHSS score between 4 to 25
	4. Intravenous rt-PA thrombolysis conducted within 4.5 h after stroke onset, if known, or the time last seen well [termed “time last known at neurologic baseline” (TLK@B)]
	5. The time to the start of administration of Study Drug must be ≤10 h after time of symptom onset or TLK@B
	6. Informed consent was signed by the subject or the legal representative
Exclusion criteria	1. Prior to stroke, significant disability exist, with modified Rankin Scale > 1 point
	2. With medical history or evidence of cerebral hemorrhage, subarachnoid hemorrhage, arteriovenous malformation, cerebral aneurysm or brain tumor
	3. With clinical or imaging evidence of contralateral cerebral infarction which is believed to have influence on the patient outcome by the investigators

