**Fig. 1 Fig1:**
[figure not shown]
Flowchart of the trial. AIS, acute ischemic stroke; SAEs, severe adverse events; IQCODE, Informant Questionnaire on Cognitive Decline in the Elderly. *If a patient is discharged within 7 days, the examination will be performed at the day of discharge

To increase the adherence to intervention protocols, all participants will receive their study drugs at the scheduled time and take the medicine under the supervision of trained nurses. Because all subjects will receive thrombolytic therapy, for safety reasons, these patients will be hospitalized for minimum of 5 days to monitor the changes in their conditions with their complete examinations such as stroke etiology and vascular status. These all will be undertaken unless the patients voluntarily request discharge or death occurs. The patients who ask to be released from the hospital within 5 days will no longer be treated with the study drugs but will be included in the modified intent-to-treat population.

Neurological statue presented as NIHSS scores will be assessed at enrollment and at 24, 48, 72 h and 7 days. Electrocardiograms will be obtained at baseline, 6 h after the study drug administration, and at 7 days. Vital signs will be monitored frequently during the period of study drug administration. Safety lab values will be assessed at enrollment and at 24, 48, 72 h and 7 days. Cranial CT examination will be performed before randomization and repeated at 24 h, 72 to 96 h, and as clinical indicated. If a participant is discharged within 7 days, the examination will be performed at the day of discharge instead.

Since glibenclamide is an active hypoglycemic agent, blood glucose levels will be checked every 2 h during the first 24 h, followed by every 4 h in the absence of any decline below 3.9 mmol/L during the period of study drug administration. In the case of hypoglycemia, blood glucose level will be corrected by administration of glucose or glucagon, as appropriate. For safety reason, if two consecutive events of hypoglycemia (< 3.9 mmol/L) or one incidence of serious hypoglycemia (< 2.2 mmol/L) occurs, the study drug will be suspended. Blood glucose and corrective glucose administration will be reported.

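### Last observation carried forward is a weak main rule for a missing 90-day mRS: day 30 is the only earlier scheduled post-stroke score, and patients lost before day 30 have no valid value to carry

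*Protocol article*

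**What the plan says.** All from the protocol article:

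- **Main rule** (Statistical analyses): "Last observation carried forward method will be used to deal with the missing data of primary outcome".
- **Second method** (same sentence): "multiple imputation method will also be used as sensitive analysis".
- **Primary outcome** (Outcome assessments, Table 2): "The ratio of mRS ≤ 2 at 90 days after the stroke onset".
- **mRS schedule** (Outcome assessments): visits at "30 ± 7 days, 90 ± 14 days (the primary end-point), 180 ± 30 days", and again at about one year.
- **In-hospital status** (Treatment, text after Fig. 1) is scored on another scale: "Neurological statue presented as NIHSS scores will be assessed at enrollment and at 24, 48, 72 h and 7 days".
- **Pre-stroke mRS** enters only through exclusion criterion 1 (Table 1): "Prior to stroke, significant disability exist, with modified Rankin Scale > 1 point". Every eligible patient therefore has a pre-stroke score of 0 or 1.
- **Analysis population** (Statistical analyses): the modified intention-to-treat set "excludes those patients who do not receive treatment or control and has no efficacy outcome data", and also drops patients found to have posterior circulation occlusion alone. The Treatment section keeps in this set patients who leave hospital within 5 days and stop study drug.

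**The concern.** Carrying an observation forward needs an earlier value of the same measure that can reasonably stand in for the missing one. Here there is at most one, at day 30.

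A patient lost between day 30 and day 90 is analysed as if nothing changed over two months. The protocol repeats the mRS at 30, 90, 180 and 360 days, so it evidently allows for change. The χ² test and the Newcombe interval would then treat the carried score as a real 90-day observation. The rule can be biased even when data are missing at random given the day-30 score.

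A treated patient lost before day 30 has no post-stroke mRS, and the rule does not say what happens. The primary efficacy conclusion depends on this rule. So does the interim decision, because the trial may stop early on the interim primary outcome.

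**Working it through.** **1. Which mRS values exist before day 90?** The mRS visits are at 30, 90, 180 and 360 days, and in-hospital assessments use the NIHSS. Only two mRS values can precede day 90: the day-30 score, and the pre-stroke score used for eligibility.

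**2. Does the analysis set remove patients with no day-30 score?** Not clearly.

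- As worded, the exclusion joins two conditions with *and*: no treatment, and no efficacy outcome data. A treated patient stays in.
- If the second condition alone were enough, a patient discharged early would still have NIHSS scores, and NIHSS improvement at day 7 is a secondary efficacy outcome. If discharge comes before day 7, the assessment is made on the day of discharge.
- The exclusion cannot mean every patient without a 90-day mRS, because the carry-forward rule would then have nothing to do.

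**3. The plan's own figure.** Inputs (Sample size estimation): 41% versus 58%, two-sided 0.05, power 80%, one O'Brien–Fleming interim at half, dropout below 10%. The pooled χ² formula gives 135 per arm. Multiplying by the two-look inflation of 1.0037 gives 136, and 136 / 0.90 = 151.1, so 152, against the stated 153. The sample size reproduces and is not in question.

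**4. Effect on the rates.** Let m be the share missing, p the true good-outcome rate, and g the share of carried values that are good. The analysed rate is q = (1 − m)p + m·g. Missing patients are assumed to be like observed ones. Power is single-look at 153 per arm. With complete data the difference is 17.0 points and power is 84.8%.

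*Day-30 score carried, m = 10% in both arms.* Assume the day-30 good rate is r times the day-90 rate, with r = 0.75 to 0.85 (not given in the document):

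- r = 0.75: placebo 0.9 × 0.41 + 0.1 × 0.3075 = 39.98%; glibenclamide 0.9 × 0.58 + 0.1 × 0.435 = 56.55%; difference 16.58.
- r = 0.85: 40.39% versus 57.13%; difference 16.75.
- The loss is 0.10 × (1 − r) × 17 = 0.26 to 0.43 points. Power is 83.0–83.7%.

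*Pre-stroke score carried (g = 1), a conditional case only:*

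- m = 5% in both arms: 0.95 × 0.41 + 0.05 = 43.95% versus 0.95 × 0.58 + 0.05 = 60.10%; difference 16.15, a loss of 0.85 points; power 81.0%.
- m = 10% in both arms: 46.9% versus 62.2%; difference 15.3, a loss of 1.7 points; power 76.9%.

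**5. No true effect, loss of 5% in one arm and 10% in the other.**

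- Pre-stroke score carried: false difference 0.05 × (1 − p), which is 2.95 points at p = 0.41 and 2.1 points at p = 0.58. Type I error is 8.1% and 6.6%.
- Day-30 score carried: false difference 0.05 × p × (1 − r), from 0.05 × 0.41 × 0.15 = 0.3 to 0.05 × 0.58 × 0.25 = 0.7 points. Type I error is 5.0–5.2%.

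**6. Standard error.** If 10% of values are imputed and carry no information, the standard error is understated by the factor √0.9 = 0.949, about 5%. A day-30 mRS does carry information about day 90, so 5% is a ceiling.

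**The case against.** The strongest reply has four parts.

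*The pre-stroke score is not the plan's rule.* A reader might infer that patients lost before day 30 automatically count as successes, because their only earlier mRS is 0 or 1. The article does not say so. It uses the pre-stroke mRS only to screen for eligibility, and the natural reading of a last observation for a post-stroke outcome is a post-stroke one. This objection stands. What remains is that the rule as written neither forbids the pre-stroke score nor names another value.

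*On the reading the text supports, the effect is small.* This also stands: less than half a point out of 17, towards no difference, with power above 80%. The larger figures need the pre-stroke reading, and the type I error figures also need unequal loss. In a double-blind trial unequal loss is possible, but nothing in the article shows it.

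*Multiple imputation is already planned.* It would expose a result that depends on the carry-forward rule. But it would do so only as a secondary check, leaving the less defensible method to decide the trial.

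*Details belong in the analysis plan.* The full imputation specification can indeed wait for that document. The choice of primary method cannot be treated as left open, because the article fixes it. Known deaths are a separate matter: 90-day mortality is collected, so a known death is not a missing outcome.

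**Conclusion.** The point holds as a criticism of the chosen primary method and of the gap before day 30. It does not show that the primary result will be materially biased.

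With low, balanced loss and day-30 scores carried, the planned difference falls by about 0.3–0.4 points. The effect becomes material only if pre-stroke scores were carried: a loss of 0.85 to 1.7 points with balanced loss of 5 to 10%, or a false difference of 2.1–3.0 points (type I error about 6.6–8%) with a 5-point imbalance and no true effect. The standard error is understated by at most about 5%.

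All sizes rest on assumed missing shares, since the article gives only a dropout rate below 10%, and on missing patients resembling observed ones. The day-30 figures also rest on the assumed ratio of 75–85%. The change is worth making because a better method is already in the plan and the present rule leaves one group of patients undefined.

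**What to change.** In Statistical analyses:

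1. Make multiple imputation the primary handling of a missing 90-day mRS, done separately by arm, with baseline and in-hospital NIHSS, age, endovascular treatment and day-30 mRS as predictors.
2. Use the same imputation model at the interim and final analyses. Keep the day-180 mRS out of it, because the interim is triggered by completion of 90-day follow-up and many patients will not yet have a day-180 score. It can be added in a sensitivity analysis at the final look.
3. Move carry-forward from day 30 to a sensitivity analysis.
4. State that the pre-stroke mRS is never carried forward, and that treated patients with no day-30 score stay in the modified intention-to-treat set and are imputed. Reword that set's exclusion so that the *and* is unambiguous.

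This needs no new data and no more patients: the predictors are already collected and the two methods swap roles. The price is a slightly wider confidence interval, and an imputation model that must be fixed before the interim look.
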